### 3.1 Primary objective

Reliability of measurement parameters for inflammation and musculoskeletal pain at consistent high workloads over time.

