#### 4.5 Power analysis

The focus of the statistical analysis is the correlation between indicators of chronic inflammation (biomarkers) and the severity of the musculoskeletal complaints in the elbow/forearm/hand-area. We are not aware of any studies on the temporal stability of blood parameters in work-related musculoskeletal pain. Therefore, the necessary knowledge to calculate an optimal amount of measurement repetitions is lacking. The present study is a preliminary study, and the number of nine (at least 6 per subject) measurement repetitions (1 / two weeks) is primarily determined by limiting the number of blood samples required in this preliminary study. Both the median and second lowest values during the measurement period will serve as indicators of the severity of chronic inflammation in the sense of a conservative approach. The correlations between the inflammation parameters and the severity of musculoskeletal pain will be calculated using the Spearman's rank correlation coefficient  $\rho$ . With 20 subjects of the exposed group, the significance limit of Spearman's  $\rho$  for a margin of error of  $\alpha$  of 10% is 0.38, which roughly corresponds to a variance clarification of ~15%. Since further clarification of our hypothesis with the methods tested here would only be meaningful if there was a clear correlation, the study achieves the required significance with a sample size of 20 subjects. The number of subjects in the unexposed control group will be equal as in the exposed group.

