### 5.2.3 Work package 3: Carrying out the measurements including data preparation

*This work package is estimated to last about 240 working days (~11 months).*

Study participation for all subjects takes about twelve to eighteen weeks, including a pre-assessment or baseline assessment at study inclusion (one visit,  $T_0$ ), and an eleven-to-seventeen-week observation period (nine visits,  $T_1$ - $T_9$ ). It is desired to start measuring the first recruited subject in “Month 8” (i.e., November 2023) of the study’s timeline and to finish measuring the last recruited subject in “Month 18” (i.e., September 2024) of the study’s timeline (cf. **Figure 2**). We assume that 25 persons have to be recruited in each group to finally have data of 20 subjects with at least 6 repeated measurements. Six repeated measurements will enable us to monitor the selected inflammation parameters for about 4 months.

The collection points at which measurements are taken are tabulated in **Table 1** and visualized in **Figure 3**.

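### Section 4.5 uses the critical value of Spearman's rho (0.38 at n=20) in place of a power calculation; a true rho of 0.38 would reach significance only about half the time

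*Protocol*

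**What the plan says.** Section 4.5 of the protocol plans the correlation between inflammation markers and pain severity, which "will be calculated using the Spearman's rank correlation coefficient". It then gives the one figure on which the number of subjects rests: "With 20 subjects of the exposed group, the significance limit of Spearman's" rho, for an alpha "of 10% is 0.38, which roughly corresponds to a variance clarification of ~15"%. It adds that further work on the hypothesis "would only be meaningful if there was a clear correlation", and concludes that "the study achieves the required significance with a sample size of 20 subjects". The synopsis, under study design and sample size calculation, carries the same text.

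The section gives no power, no numerical value for a clear correlation, and no statement on whether alpha is one- or two-sided. The analysed number stays at 20 after dropout, because section 5.2.3 says: "We assume that 25 persons have to be recruited in each group to finally have data of 20 subjects".

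**The concern.** The conclusion does not follow from the figure. Every sample size has a critical value, so quoting one cannot show that a particular sample size suffices. What would show it is the probability of crossing that limit when a stated true correlation exists. The section carries the heading of a power analysis but does not give that probability.

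The only magnitude offered is 0.38, or about 15% of variance, and the text moves from it directly to adequacy. A reader will take it that 20 subjects can be relied on to show a correlation of that order. The practical risk is a misread null: a non-significant result could be reported as evidence that no clear correlation exists, although the study would miss a true rho of 0.38 about as often as it finds it.

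**Working it through.** **Inputs.** n = 20, alpha = 10%, Spearman's rho and the limit of 0.38 all come from section 4.5. Two things are assumed: a two-sided test, because only that reproduces 0.38, and bivariate normal data for the simulations.

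**Step 1: reproduce the protocol's figure.** The critical value is r = t / √(n − 2 + t²), with t the 95th percentile on 18 degrees of freedom.

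- Two-sided 10%: 0.378. The simulated 95th percentile of Spearman's rho under no correlation is 0.379.
- One-sided 10%: 0.299. Two-sided 5%: 0.444. Neither matches.
- 0.38² = 0.144, which agrees with the stated figure of about 15%.

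So 0.38 is right as a two-sided 10% critical value.

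**Step 2: power if the true rho is 0.38.** On the Fisher scale, power ≈ Φ(atanh(rho)/SE − 1.645). SE is √(1/17) = 0.2425, or √(1.06/17) = 0.2497 with the usual Spearman correction; atanh(0.38) = 0.400.

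- 0.400/0.2425 − 1.645 = 0.005, so power is 50%.
- 0.400/0.2497 − 1.645 = −0.043, so power is 48%.
- Simulation: 50% if 0.38 is the population Spearman value, 47% if it is the underlying Pearson value.

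**Step 3: power at other true values, n = 20.** The simulation column treats the true value as a population Spearman rho. The range covers both Fisher versions and both simulations.

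| True rho | Share of variance | Power (simulation) | Range over methods |
|---|---|---|---|
| 0.38 | 14% | 50% | 47-50% |
| 0.50 | 25% | 72% | 69-73% |
| 0.55 | 30% | 81% | 78-82% |

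**Step 4: correlation detectable with 80% power.** rho = tanh((1.645 + 0.842) × SE), which gives 0.54 or 0.55 for the two SEs. The square of 0.55 is 0.30, about twice the share of variance that the protocol mentions.

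**Step 5: subjects needed for 80% power at 0.38.** n = v × ((1.645 + 0.842)/0.400)² + 3, with v = 1 or 1.06, gives 42 or 44. This shows the size of the gap; it is not a proposal to enlarge the study.

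**Step 6: precision.** An observed rho of 0.38 with n = 20 has a 90% interval of tanh(0.400 ± 1.645 × SE): 0.00 to 0.66, or −0.01 to 0.67 with the correction.

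**The case against.** The strongest defence is that the protocol says nothing false about 0.38. It calls it a significance limit, which it is, and never calls it a detectable or target effect. What counts as a clear correlation is left without a number; if about 0.55 was meant, 20 subjects give about 80% power. The study is preliminary and observational, and section 3 calls the correlation analysis exploratory. All of this stands, and it makes the point a faulty inference rather than an arithmetic error. It does not rescue the concluding sentence, because the protocol names no such target and the only magnitude it offers is the limit itself.

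Three stronger readings are tempting, and the protocol does not support them.

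- **That a true association would be abandoned half the time.** A reader might infer a go/no-go rule at p<0.10 from the remark on when further work is meaningful. No such rule is written. Section 5.1 plans the follow-up funding application without condition, and section 5.2.5 has it drafted in parallel with publication. The half also refers to one test. The plan has three markers, each with two summaries (median and second lowest). If all three markers truly had rho 0.38 and intercorrelated at 0.2 to 0.8 (an assumption), the chance that at least one reaches the limit would be about 68-85%. If only one marker is associated, about 50% remains.
- **That the primary objective is wrongly sized.** Section 3.1 names "Reliability of measurement parameters for inflammation and musculoskeletal pain at consistent high workloads over time", while section 4.5 discusses only the correlation. But section 4.5 openly says that the knowledge needed to optimise the number of repetitions is lacking, and that blood sampling limits them. A figure for reliability precision would rest on an assumed intraclass correlation that the protocol does not give, and that detail may properly sit in an analysis plan.
- **That the design needs other analyses.** Pooling both groups for reliability would not fit an objective defined at high workload. A within-person correlation would answer a different question from the per-person summaries that the section specifies.

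**Conclusion.** The concluding sentence of section 4.5, and its copy in the synopsis, is wrong as written. The critical value is correct, but it cannot support the claim that 20 subjects suffice. For one marker-pain correlation tested at two-sided 10%, power is about one half (47-50%) at a true rho of 0.38, and 80% is reached only at about 0.55.

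The figures rest on n = 20 analysed, a two-sided test and bivariate normality. The choice of approximation moves them by only a few percentage points. This is a should-fix matter of wording: the study claims a property that it does not have, but its design, its primary objective and its planned follow-up do not depend on that claim.

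**What to change.** Replace the concluding sentence in section 4.5 and in the synopsis with, for example:

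> With n=20 and two-sided alpha 10%, an observed rho of at least 0.38 is significant. For a single correlation, the study has about 50% power for a true rho of 0.38 and 80% power for about 0.55. A non-significant result does not exclude a correlation of 0.38.

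In the same paragraph, say which true rho counts as clear, and state that the correlation will be interpreted by its estimate and confidence interval. If no target can be justified, present n=20 as a feasibility choice and give the precision it yields (for example, the interval of about 0 to 0.67 around an observed 0.38).

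The cost is a few sentences in two places. No participants, visits or analyses are added; the stated capability becomes less favourable but correct.

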## 5 Study procedure

### 5.1 Study duration

Total study duration is expected to last about 30 months (~2.5 years). The study consists of several work packages, which are displayed in **Figure 2**. Each work package is explained in more detail in the following subchapter.

Gaining an ethical approval for the study is not part of the study duration and, therefore, not identified as a separate work package. After ethical approval, the study may start by selecting and recruiting the study population. Recruitment is carried out through existing contacts via occupational physicians from companies with corresponding work-related exposures. We have already received a letter of intent from two occupational medicine services (Bosch and Mercedes-Benz AG). Only employees from plants in the area of Tübingen (max. 75 min by car) will be recruited and data collection will be carried out by employees of the Institute of Occupational medicine and Health Services Research and external physicians.

As soon as the 30-month period is finished, it is planned to apply for external funding for a follow-up cohort study by the German Research Foundation's (DFG) Individual Research Grant (*Sachbeihilfe*).

| year  | 2023 |     |     |     |     |     |     |     |     |     | 2024 |     |     |     |     |     |     |     |     |     |     |     | 2025 |     |  |
|-------|------|-----|-----|-----|-----|-----|-----|-----|-----|-----|------|-----|-----|-----|-----|-----|-----|-----|-----|-----|-----|-----|------|-----|--|
| Month | Apr  | May | Jun | Jul | Aug | Sep | Oct | Nov | Dec | Jan | Feb  | Mar | Apr | May | Jun | Jul | Aug | Sep | Oct | Nov | Dec | Jan | Feb  | Mar |  |
|       | 1    | 2   | 3   | 4   | 5   | 6   | 7   | 8   | 9   | 10  | 11   | 12  | 13  | 14  | 15  | 16  | 17  | 18  | 19  | 20  | 21  | 22  | 23   | 24  |  |
| WP 1  |      |     |     |     |     |     |     |     |     |     |      |     |     |     |     |     |     |     |     |     |     |     |      |     |  |
| WP 2  |      |     |     |     |     |     |     |     |     |     |      |     |     |     |     |     |     |     |     |     |     |     |      |     |  |
| WP 3  |      |     |     |     |     |     |     |     |     |     |      |     |     |     |     |     |     |     |     |     |     |     |      |     |  |
| WP 4  |      |     |     |     |     |     |     |     |     |     |      |     |     |     |     |     |     |     |     |     |     |     |      |     |  |
| WP 5  |      |     |     |     |     |     |     |     |     |     |      |     |     |     |     |     |     |     |     |     |     |     |      |     |  |

**FIGURE 2. SCHEMATIC STUDY DURATION DIVIDED INTO INDIVIDUAL WORK PACKAGES (WP).**

## 5.2 Work packages

### 5.2.1 Work package 1: Selection and recruitment of study population

*This work package is estimated to last about 60 working days (~3 months).*

Contact with Daimler AG and Robert Bosch, in particular their occupational physicians, to select potentially suitable workplaces. We will perform site visits for applying rough workload analyses to estimate whether the selected workplaces are eligible for inclusion. Information meetings and agreements with both companies (including agreement of their Work Council) will be set up in accordance with the occupational physicians for recruitment and information meetings with the employees participating in the study.

### 5.2.2 Work package 2: Preparation of measurement procedures

*This work package is estimated to last about 125 working days (~5 months).*

In this period, two methods used for determining exposure at work are selected. Five ergonomic assessment tools are evaluated as based on the literature, and two methods are determined for the study. Based on several video sequences of work in the workplaces of the participating companies, the experimental observers are trained to use the two methods and determine the workload of the workplaces. Depending on the work situation, the observation time has to be adapted to the work content and work organization.

### 5.2.3 Work package 3: Carrying out the measurements including data preparation

*This work package is estimated to last about 240 working days (~11 months).*

Study participation for all subjects takes about twelve to eighteen weeks, including a pre-assessment or baseline assessment at study inclusion (one visit,  $T_0$ ), and an eleven-to-seventeen-week observation period (nine visits,  $T_1$ - $T_9$ ). It is desired to start measuring the first recruited subject in “Month 8” (i.e., November 2023) of the study’s timeline and to finish measuring the last recruited subject in “Month 18” (i.e., September 2024) of the study’s timeline (cf. **Figure 2**). We assume that 25 persons have to be recruited in each group to finally have data of 20 subjects with at least 6 repeated measurements. Six repeated measurements will enable us to monitor the selected inflammation parameters for about 4 months.

The collection points at which measurements are taken are tabulated in **Table 1** and visualized in **Figure 3**.

### 5.2.4 Work package 4: Data analysis

*This work package is estimated to last about 80 working days (~4 months).*

In this preliminary study, only a small sample with a high occupational exposure will be included. This means that the effects of different levels of occupational physical exposure itself cannot be statistically tested. The interest is in the strength of the correlations between inflammatory parameters in the blood and intensity of the musculoskeletal pain. Further, for all parameters collected (workload, inflammation parameters in the blood, musculoskeletal symptoms, findings in the functional tests), the degree of constancy over the eleven to seventeen weeks is investigated in order to gain evidence on the reliability of the measurement procedures with regard to a long-term study. In addition, a general comparison of biomarker concentration to a unexposed control group will further help in identifying the potentials of a future long-term study. The measurement variables are shown in **Table 1**.

#### 5.2.5 Work package 5: Publication and external follow-up funding

*This work package is estimated to last about 60 working days (~3 months).*

The study results are published at congresses and in a peer-reviewed journal. Parallel, study results are used to start writing a DFG Individual Research Grant (*Sachbeihilfe*) for funding a follow-up cohort study.

### 5.3 Study outcomes

The study will include a large number of measurement parameters in order to determine a few optimally selected measurement parameters for the planned elaborate long-term cohort study. An overview is presented in **Table 1**.

**TABLE 1.** OVERVIEW OF THE INCLUDED MEASUREMENT PARAMETERS AND COLLECTION POINTS.

| Method                                           | Parameter                                                                                                                                                                                                                            | Time point                                                                                                                     |
|--------------------------------------------------|--------------------------------------------------------------------------------------------------------------------------------------------------------------------------------------------------------------------------------------|--------------------------------------------------------------------------------------------------------------------------------|
| Exposure at work                                 | Determining the hand activity                                                                                                                                                                                                        | Inclusion (T 0 )                                                                                                    |
|                                                  | Level and variability of workload determined using two standardized methods: the observation methods are determined based on literature (Klußmann et al., 2010; Takala et al., 2010) and video analyses of the respective workplaces | 11-to-17-week observation period (T 1 , T 4 , T 7 , T 9 )                          |
| General medical examination for inclusion        | Anamnesis                                                                                                                                                                                                                            | Inclusion (T 0 )                                                                                                    |
|                                                  | Frequency and intensity of perceived musculoskeletal discomfort in elbows, forearms and hands with the Cornell Musculoskeletal Discomfort Questionnaire (Kreuzfeld et al., 2016)                                                     |                                                                                                                                |
|                                                  | Differential blood test                                                                                                                                                                                                              |                                                                                                                                |
| Pain provocation                                 | Medical examination according to the current procedure employed by the DGUV                                                                                                                                                          | After weekly blood sample (T 1 -T 9 )                                                                    |
|                                                  | Pain triggering at low or strong force for four directions and two rotations of the hands                                                                                                                                            |                                                                                                                                |
|                                                  | Pressure pain by means of pressure pain threshold (PPT) on left & right epicondyles lateralis & medialis and carpal tunnel                                                                                                           |                                                                                                                                |
| Numeric rating scale on rating of perceived pain | Pain intensity at night, during the working week (maximum and minimum), current pain                                                                                                                                                 | Before weekly blood sample (T 1 -T 9 )
Last working day of the week (T 1 -T 9 ) |
| Inflammation parameters in blood                 | Level and variability of the concentration of CRP, IL-6, IL-1 $\beta$ by a blood sample taken at the same time of the day                                                                                                            | 11-to-17week observation period (T 1 -T 9 ), randomized by weekday                                       |

|                                                                 |                                                                             |                                                                                                       |
|-----------------------------------------------------------------|-----------------------------------------------------------------------------|-------------------------------------------------------------------------------------------------------|
| Symptoms and signs of upper extremity musculoskeletal disorders | Medical examination according to the current procedure employed by the DGUV | 11-to-17-week observation period (T 1 , T 4 , T 7 , T 9 ) |
|-----------------------------------------------------------------|-----------------------------------------------------------------------------|-------------------------------------------------------------------------------------------------------|

## 5.4 Participant timeline

The timeline of the participant, i.e. what measurements are performed when, is visually presented in **Figure 3**. When exposure at work and general medical examination fulfil the eligibility criteria, the participant is enrolled in the study after informed consent. This screening appointment is expected to last about max. 1.5 h. During the 11-to-17-week observation period the weekly measurements (blood sample, musculoskeletal pain rating, pressure pain and pain provocation by movement, and musculoskeletal discomfort questionnaire) will last about 20 min and will take place directly before the individual working shift. On four occasions (T1, T4, T7, and T9) an additional 10 min will be necessary for assessing symptoms and signs of upper extremity musculoskeletal disorders.

[figure not shown]

**FIGURE 3.** PARTICIPANT TIME-FLOW INCLUDING TWO-WEEKLY COLLECTION POINTS.

